#### Secondary endpoints

2.8.2

*Anthropometrics:* This mainly includes body mass index (BMI) and waist-to-hip ratio (WHR). At each visit, body weight and waist and hip circumferences will be measured using a standardized stadiometer and a calibrated electronic scale.

*Serum markers:* Alanine aminotransferase (ALT), aspartate aminotransferase (AST), γ-glutamyl transferase (GGT), fasting insulin, glucose, markers of inflammation (IL-6, CK18), lipid profile (total cholesterol (TC), low-density lipoprotein (LDL), high-density lipoprotein (HDL), and triglyceride (TG) will be assayed. Insulin resistance (HOMA-IR) was calculated using measurements for fasting glucose and fasting insulin. Hepatocyte apoptosis is a major mechanism of NAFLD progression, and cytokeratin-(CK-)18 is a marker derived from hepatocyte apoptosis produced by caspase3, which is significantly higher in patients with NAFLD than those without NAFLD.^[29,30]^ Importantly, in 2 large randomized controlled trials of children and adults, serum CK18 levels were significantly reduced with improved liver histology after treatment.^[31]^ These findings suggest that serum CK18 fragments may be an attractive biomarker for monitoring response to different therapeutic agents.^[32]^

*Quality of Life:* We will use SF-36 Life Scale to assess subjects.

#### Safety endpoints

2.8.3

The safety of formulated food will be assessed on the basis of AE, clinical laboratory tests, physical examination, and vital signs. Clinical laboratory tests include liver, kidney, urine routine, glucose metabolism, lipid metabolism, electrocardiogram (ECG), and the like.

#### Exploratory end point

2.8.4

*Stool samples:* Changes of intestinal flora abundance and diversity at 24 weeks.

### Data

2.9

All the data will be entered by 2 persons and managed by the hospital's electronic data collection system. They will be kept confidential and only relevant personnel can view them. The data regulator will check them. They are independent of the sponsor and have no conflict of interest. The final data can be contacted with the sponsor after the trial is over.

### Sample size estimation

2.10

The sample size was calculated using Medcalc version 18.2.1 software. On the basis of the results of the pre-test, we expected the formulated food to improve the ratio by about 50% and about 13% in the placebo group, with an α level of 2-sided type I error of 0.05, with a β level of type II error of 0.02. The placebo group was calculated to be 35 patients. Because the formulated food group vs the placebo group is 2:1, the total number is about 120 taking into account the 10% shedding rate.

### Statistical analyses

2.11

This study will use intent-to-treat patient population. Values with a bias distribution will be log transformed before analysis. Baseline characteristics, categorical variables will be tested by χ^2^, and continuous variables will be compared by *t* test. Repeated measures analysis of variance (ANOVA) will be used for variables measured over time to test treatment efficacy, time, and interaction between them. To compare differences between baseline and 24 weeks, paired *t* tests will be used for primary and secondary outcomes (liver function biomarkers, diabetic biomarkers, liver fat content, diabetic biomarkers, lipid biomarkers, BMI, WHR). Secondary analysis will be performed in all participants who completed 24 weeks of intervention and had a drug intake rate of ≥80%, and cases with missing data would be excluded from the analysis. In all analyses, a 2-sided *P* value 0.05 will be considered significant. The frequency of the AE will be assessed using a χ^2^ test.

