**Methods::**

The study plan to recruit adult patients (18–75 years, n = 120) with NAFLD, range of alanine aminotransferase is 1.5 to 5 times upper limit of normal (ULN) or liver biopsy is confirmed as NASH. Participants will be randomly allocated into 2 groups: formulated food (n = 80) and a placebo group (n = 40) for 24 weeks. Both groups will receive lifestyle and nutritional advice. The primary endpoint is a decrease in MRS-PDFF by more than 30% from baseline at 24 weeks. The secondary endpoints include the change of anthropometric, liver function, glycolipid metabolism, and systemic inflammation at 4, 12, and 24 weeks. In addition, we consider the changes in intestinal microbiota as an exploration to assess the abundance and diversity at 24 weeks. Weeks 24 to 36 are the follow-up period of drug withdrawal.

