### Study flow and schedule

2.4

The flow chart of the study is shown in Figure 1, and the study schedule is summarized in Table 3. For study visits at week 0, week 4, week 12, week 24, week 36 patients must fast for 8 hours before the visit, and then take blood for metabolic assessment. Body weight, waist circumference, and hip circumference will be measured at each visit. In order to better assess patient compliance, we require that remaining meal powders be returned at each study visit and will be counted by drug administrators to further reduce the likelihood of unblinding.

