**Figure 1 F1:**
[figure not shown]
Study design.

**Table 3 T3:** Objectives and procedures.

	Study time point, wk				
	Treatment period				Follow-up period
Study objectives	0	4	12	24	36
Primary objectives					
Change in liver fat content (MRS/MRI-PDFF)	×		×	×	
Secondary objectives					
Change in anthropological indicators (BMI and WHR)	×	×	×	×	×
Change in liver function (ALT, AST, GGT)	×	×	×	×	×
Change in diabetic factors (FPG, FINS, HOMA-IR, HbA1c)	×	×	×	×	×
Change in lipids (TG, TC, HDL-C, LDL-C)	×	×	×	×	×
Change in IL-6 and CK18	×	×	×	×	×
Change in HRQOL (SF-36)	×			×	
Assessment of diet and exercise	×	×	×	×	
Record distribute and recycle of drug	×	×	×	×	
Record of drug combination	×	×	×	×	
Safety objectives					
Renal function (BUN, Cr, eGFR)	×	×	×	×	×
Blood routine	×	×	×	×	×
Urine routine	×	×	×	×	×
Fecal routine	×				
Coagulation function	×				
TSH	×				
Virus	×				
Blood HCG	×				
ECG	×			×	
Exploratory endpoint					
Change in intestinal flora	×			×	

All objectives will be compared between formulated food and placebo. ALT = alanine aminotransferase, AST = aspartate aminotransferase, BMI = body mass index, CK18 = cytokeratin 18, Cr = creatinine, eGFR = estimated glomerular filtration rate, ECG = Electrocardiogram, FINS = fasting insulin, FPG = fasting plasma glucose, GGT = γ-glutamyl transferase, HbA1c = glycosylated hemoglobin A1c, HCG = human chorionic gonadotropin, HDL-C = high-density lipoprotein-cholesterol, HOMA-IR = homeostasis model assessment insulin resistance, HRQOL = health-related quality of life, IL-6 = interleukin-6, LDL-C = low-density lipoprotein-cholesterol, PDFF = proton density fat fraction, TC = total cholesterol, TG = triglycerides, TSH = thyroid-stimulating hormone, WHR = waist to hip ratio.

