#### Primary endpoints

2.8.1

The study endpoints are summarized in Table 4. The primary endpoint is a decrease in MRS-PDFF by more than 30% from baseline at 24 weeks. MRS-PDFF and MRI-PDFF are closely related to liver fat content assessed by liver biopsy, with no superiority between them. Preliminary results from a phase II clinical trial confirmed the feasibility of MRI-PDFF in longitudinal observation of clinical trials and highlighted the evidence that liver stiffness by MRI-PDFF is a biomarker of steatosis. In addition, data confirm that changes in MRI-PDFF are associated with hepatic steatosis and overall NAS score response. At the same time, MRI achieves 100% accuracy by a fat fraction threshold of 5.56% to distinguish normal and abnormal fat fractions in liver steatosis testing as long as all known confounding factors are resolved. Therefore, MRS-PDFF and MRI-PDFF potentially replace liver biopsy to assess liver fat content.^[26–28]^

**Table 4 T4:** Study endpoints.

Primary endpoints
<Efficacy endpoints>
Change in liver fat content (MRS/MRI-PDFF) from baseline at 24 wks
Secondary endpoints
<Efficacy endpoints>
Change in anthropological indicators (BMI, WHR) from baseline at 4,12,24 wks and at the time of drug discontinuation
Change in liver function biomarkers (ALT, AST, GGT) from baseline at 4,12, 24 weeks and at the time of drug discontinuation
Change in diabetic biomarkers (FPG, FINS, HOMA-IR, HbA1c) from baseline at 4,12, 24 wks and at the time of drug discontinuation
Change in lipid biomarkers (TG, TC, HDL-c, LDL-C) from baseline at 4,12, 24 wks and at the time of drug discontinuation
Change in IL-6 and CK18 from baseline at 4,12, 24 wks and at the time of drug discontinuation
Change in HRQOL using SF-36 from baseline at 24 wks
< Safety endpoints>
Change in blood tests of renal function (BUN, Cr, eGFR) from baseline at 4,12,24 wks
< Exploratory endpoint>
Changes of intestinal flora abundance and diversity from baseline at 24 wks

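### The only named between-arm efficacy analysis, repeated measures ANOVA, uses no baseline covariate and gives no week-24 arm contrast; its treatment main effect is probably diluted

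*Protocol article*

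**What the plan says.** Section 2.11 (Statistical analyses) states: "Repeated measures analysis of variance (ANOVA) will be used for variables measured over time to test treatment efficacy, time, and interaction between them". It does not list the visits that enter the model and names no covariate. For baseline against week 24, paired t "tests will be used for primary and secondary outcomes".

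Table 3 (section 2.4) fixes when outcomes are measured:

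- The row "Change in liver fat content (MRS/MRI-PDFF") is marked at weeks 0, 12 and 24.
- BMI/WHR, liver enzymes, glucose and lipid markers, IL-6 and CK18 are marked at weeks 0, 4, 12, 24 and 36. Section 2.4 confirms the blood visits: "For study visits at week 0, week 4, week 12, week 24, week 36 patients must fast for 8 hours before the visit".
- SF-36 is marked at weeks 0 and 24 only.

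The abstract says of the last interval: "Weeks 24 to 36 are the follow-up period of drug withdrawal".

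Table 4 (section 2.8.1) words the efficacy endpoints as changes, for example "Change in liver function biomarkers (ALT, AST, GGT) from baseline at 4,12, 24 weeks and at the time of drug discontinuation". The text of section 2.8.1 defines the primary endpoint as a responder: "The primary endpoint is a decrease in MRS-PDFF by more than 30% from baseline at 24 weeks".

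**The concern.** The endpoints ask how the arms differ in change from baseline at named weeks, above all week 24. Neither term of the planned ANOVA answers that directly.

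- **Main effect.** If week 0 is a level of the time factor, the treatment term averages the arm difference over all visits. One of these is week 0, where randomisation makes the expected difference zero. If week 36 also enters, the average includes a visit after the product has been withdrawn. Yet this is the term that the sentence ties to efficacy.
- **Interaction.** It asks whether the arm profiles diverge anywhere, with 2 degrees of freedom for PDFF and 4 for five-visit markers. It gives no single effect estimate.
- **Paired t tests.** They compare each patient with himself or herself, so they do not compare arms.

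Baseline is measured for every efficacy outcome but is not named as a covariate, which is where it would add most precision. At stake are power and a readable week-24 estimate for the continuous outcomes.

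**Working it through.** **The plan's own figure.** Section 2.10 sizes the trial on two proportions: "we expected the formulated food to improve the ratio by about 50% and about 13% in the placebo group". With two-sided alpha 0.05, beta 0.02, 2:1 allocation, pooled variance and no continuity correction, this gives 35 placebo and 105 in total. Then 105/0.90 = 117, against the stated 35 and about 120. The figure reproduces and does not depend on the ANOVA.

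**Step 1: what the main effect targets.** The main effect is the mean of the arm differences over the visits entered. Take the week-24 effect as 1. The time courses are assumptions; the documents give none.

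| Outcome, visits entered | Assumed effect by visit | Mean |
|---|---|---|
| PDFF: 0, 12, 24 | 0, 1, 1 (constant) | 2/3 = 67% |
| PDFF: 0, 12, 24 | 0, 1/2, 1 (linear rise) | 1.5/3 = 50% |
| Five-visit: 0, 4, 12, 24, 36 | 0, 1, 1, 1, 1 (constant, kept) | 4/5 = 80% |
| Five-visit | 0, 1, 1, 1, 0 (constant, lost at 36) | 3/5 = 60% |
| Five-visit | 0, 1/6, 1/2, 1, 1/2 (linear, half kept) | 2.17/5 = 43% |
| Five-visit | 0, 1/6, 1/2, 1, 0 (linear, lost at 36) | 1.67/5 = 33% |

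**Step 2: illustrative power for PDFF.** Inputs: 80 and 40 randomised less 10% leaves 72 and 36, so f = 1/72 + 1/36 = 0.04167. Assumed: effects 0, 0.3 and 0.6 SD at weeks 0, 12 and 24, and compound symmetry with correlation r.

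- Main effect: mean 0.3, variance f(1+2r)/3. At r = 0.5 the SE is 0.1667 and z = 1.80, so power = Φ(1.80 − 1.96) = 0.44.
- Interaction (2 df): the squared deviations from the mean sum to 0.18, and the noncentrality is 0.18/[(1−r)f]. At r = 0.5 this is 8.64, giving power 0.753 (noncentral chi-square).
- Week-24 ANCOVA: variance f(1−r²). At r = 0.5 the SE is 0.1768 and z = 3.39, so power = Φ(3.39 − 1.96) = 0.924.

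| r | Main effect | Interaction | Week-24 ANCOVA |
|---|---|---|---|
| 0.5 | 0.44 | 0.753 | 0.924 |
| 0.6 | 0.40 | 0.846 | 0.957 |
| 0.7 | 0.38 | 0.935 | 0.984 |

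If the full 0.6 SD is already present at week 12, the main effect still reaches only 67% to 59% over the same range of r.

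**Step 3: a case where the ranking reverses.** Five visits, 0.6 SD at weeks 4, 12 and 24, none at week 36, r = 0.5. The mean is 0.36 and the squared deviations sum to 3(0.24²) + 2(0.36²) = 0.432. The noncentrality is 0.432/0.02083 = 20.7 on 4 df, giving interaction power of 97% against 92% for week-24 ANCOVA.

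**Step 4: a smaller assumed effect.** At 0.5 SD with r from 0.3 to 0.8, PDFF main-effect power is 26–61% and week-24 ANCOVA 73–98%.

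**The case against.** **The visits are inferred.** Section 2.11 does not say that week 0 or week 36 is an outcome level. A reader might infer that the plan states this; it does not. Table 4 words the endpoints as changes from baseline; if changes were analysed, week 0 would not be a level and its dilution would not arise. For week 36 the inference is weaker still: the abstract lists secondary endpoints at weeks 4, 12 and 24, and the Table 4 reference to discontinuation is ambiguous. This stands, and the point is worded accordingly.

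**A condensed article may leave such detail to the full protocol or analysis plan.** This stands for the visit list. It does not remove the point: the article does commit to a named method, and neither of the terms it names as tests of treatment is a week-24 arm contrast.

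**The interaction is planned too.** A reader might infer that the whole ANOVA is diluted or badly underpowered. The documents do not support that. With baseline as a level, the interaction carries the treatment effect undiluted. It can be weaker than week-24 ANCOVA (75% against 92%), close to it (93.5% against 98%) or stronger (97% against 92%). Fading of the effect by week 36 dilutes the main effect but can strengthen the interaction.

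**The primary endpoint.** A reader might also infer that the primary result or the sample size is undermined. The primary endpoint is a week-24 responder rate and the sample size rests on two proportions, so neither is touched. Week 36 does not concern PDFF, which is not measured then.

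**Conclusion.** The point holds in a limited form. Section 2.11 names repeated measures ANOVA as its only between-arm efficacy analysis, with no baseline covariate and no week-24 contrast. On the natural reading of Table 3, the treatment main effect is diluted, to 50–67% of the week-24 effect for PDFF and roughly 33–80% for five-visit markers. The upper end of the latter applies only if the effect is constant and fully kept at week 36.

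The dilution concerns the main effect alone. The weakness of the interaction is that it is omnibus and yields no week-24 estimate; its power has no fixed ranking against ANCOVA. All power figures rest on an assumed effect size, correlation and time course, because the documents give no SD, correlation or profile. The matter affects the continuous outcomes and should be corrected, but it does not threaten the responder endpoint or the stated sample size.

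**What to change.** For continuous outcomes, replace the ANOVA sentence with a repeated measures model:

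- Outcomes: the post-baseline on-treatment visits only (weeks 12 and 24 for PDFF; weeks 4, 12 and 24 for BMI/WHR and the blood markers).
- Terms: arm, visit, arm-by-visit, and the baseline value as covariate.
- Efficacy result: the week-24 between-arm difference with its 95% CI.
- SF-36, measured only at weeks 0 and 24: ANCOVA on the baseline value.
- Week 36: a separate between-arm contrast, labelled off-treatment.

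The cost is wording only. All the data are already scheduled in Table 3, and neither the sample size nor any visit changes. The text can be settled before unblinding, since section 2.7 keeps the blind until all subjects have completed 36 weeks.

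### The test named for the primary outcome is a paired t test, while the endpoint and the sample size call for a between-arm comparison of responder rates that no stated test plainly supplies

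*Protocol article*

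**What the plan says.** All references are to the protocol article.

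- **Endpoint.** Section 2.8.1: "The primary endpoint is a decrease in MRS-PDFF by more than 30% from baseline at 24 weeks". The abstract says the same. This is a yes/no response for each patient.
- **Table 4** lists the primary endpoint differently, as a continuous quantity: "Change in liver fat content (MRS/MRI-PDFF) from baseline at 24 wks".
- **Sample size.** Section 2.10: "we expected the formulated food to improve the ratio by about 50% and about 13% in the placebo group", with two-sided alpha 0.05, beta 0.02, 2:1 allocation, 35 placebo patients before dropout, and about 120 in total after a 10% allowance.
- **Analysis.** Section 2.11: "To compare differences between baseline and 24 weeks, paired *t* tests will be used for primary and secondary outcomes". The list that follows includes liver fat content.
- **Other tests in section 2.11.** "Repeated measures analysis of variance (ANOVA) will be used for variables measured over time to test treatment efficacy, time, and interaction between them". For baseline: "Baseline characteristics, categorical variables will be tested by χ^2^, and continuous variables will be compared by *t* test". For adverse events: "The frequency of the AE will be assessed using a χ^2^ test".
- **Intent.** The Table 3 footnote says that every objective is to be compared between food and placebo, but names no test.
- **Co-intervention.** Abstract: "Both groups will receive lifestyle and nutritional advice".

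**The concern.** The only sentence that links a test by name to the primary outcome gives one that compares each patient with his or her own baseline. It answers whether liver fat changed, not whether it changed more on the formulated food than on placebo. It also cannot be run on responder status, which has no baseline value.

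This matters because both arms receive dietary advice and an exercise target, so some improvement in both is to be expected. A within-arm test credits that improvement to the product. The 2:1 allocation adds a second hazard. For the same true change, the arm of 80 reaches significance more often than the arm of 40, so two paired tests set side by side can suggest a difference that does not exist. The power on which the trial was sized belongs to a comparison that section 2.11 does not plainly name.

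**Working it through.** **1. Which test was the trial sized for?** Inputs from section 2.10: p1 = 0.13 (placebo), p2 = 0.50 (food), ratio k = 2, two-sided alpha 0.05 (z = 1.960), beta 0.02 (z = 2.054). The pooled two-proportion formula for the placebo arm is

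n = [z(α/2)·√(p̄(1−p̄)(1+1/k)) + z(β)·√(p1(1−p1) + p2(1−p2)/k)]² / (p2−p1)²

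- p̄ = (0.13 + 2 × 0.50)/3 = 0.3767
- first root: √(0.3767 × 0.6233 × 1.5) = 0.5935
- second root: √(0.1131 + 0.125) = 0.4880
- n = (1.960 × 0.5935 + 2.054 × 0.4880)² / 0.37² = 34.25, rounded up to 35

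This is the plan's own figure. With 70 food patients the total is 105, and 105/0.90 = 116.7, or 117, consistent with about 120. The design therefore rests on a between-arm comparison of responder proportions.

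**2. Does section 2.11 contain that comparison?**

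| Test named | Stated use | Between-arm test of the responder rate? |
|---|---|---|
| Paired t | primary and secondary outcomes, week 24 against baseline | No: within-patient, continuous |
| Repeated measures ANOVA | variables measured over time | No: between-arm, but for continuous values |
| χ² | baseline characteristics, on the plain reading | Not stated |
| χ² | adverse event frequency | No |

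Table 3 schedules PDFF at weeks 0, 12 and 24, so the treatment-by-time term of the ANOVA could compare continuous liver fat between arms. That fits the Table 4 endpoint but not the section 2.8.1 endpoint. Nothing says which analysis decides.

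**3. What can a paired test show with no product effect?** Assumption, not in the documents: both arms share a mean fall of d SDs of the within-patient change. The probability of a significant fall comes from the noncentral t distribution with n − 1 degrees of freedom and noncentrality d√n, two-sided 0.05. The last column is P(food significant) × [1 − P(placebo significant)].

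| d | Food significant (n = 80) | Placebo significant (n = 40) | Food significant, placebo not |
|---|---|---|---|
| 0 | 2.5% | 2.5% | 2.4% |
| 0.1 | 14% | 9% | 13% |
| 0.2 | 42% | 23% | 32% |
| 0.3 | 76% | 46% | 41% |
| 0.4 | 94% | 69% | 29% |
| 0.5 | 99% | 87% | 13% |
| 0.8 | >99.9% | 99.8% | about 0.1% |

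Allowing for 10% dropout (72 and 36) changes little: the last column at d = 0.2, 0.3 and 0.4 becomes 30%, 41% and 33%.

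**4. Do the planned numbers support the between-arm test?** For 13% against 50%, two-sided 0.05, power is 98.2% at 35/70 and 98.5% at 36/72 (120 less 10%). Exact power at 36/72 is 98.4% for the uncorrected χ² and 97.9% for Fisher's test. With a common rate of 13%, the exact type I error at 36/72 is 4.6% and 3.2% respectively.

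**The case against.** The strongest reply is that the plan does contain a between-arm efficacy test. The ANOVA is meant to test treatment and its interaction with time, liver fat is measured three times, and Table 4 gives the primary endpoint as a continuous change. On that reading an improvement shared by both arms does not bias the treatment comparison, and the Table 3 footnote confirms that a comparison of arms is intended.

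Much of this stands. A reader might infer that the paired t test is the only efficacy test, or that the plan abandons its randomised control. The documents support neither. They leave two candidate analyses and two versions of the endpoint, with no rule for choosing. What the reply does not supply is a test of the responder rate, which section 2.8.1 makes primary and section 2.10 uses for the sample size.

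Three further limits apply.

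- The plan nowhere defines success as significance in the food arm and not in placebo, so the last column of the table matters only if results are read that way.
- The χ² sentence on baseline characteristics is garbled and could be stretched to cover all categorical variables, although baseline is the plain reading.
- A reader might add regression to the mean from entry on raised ALT. ALT is a secondary outcome, biopsy is an alternative route of entry with no split given, and PDFF is not an entry criterion. That argument does not carry over to the primary endpoint.

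The point is not a detail left to a separate analysis plan, because section 2.11 does name a test for the primary outcome and it does not fit.

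**Conclusion.** The concern holds as a mismatch between endpoint, sample size and stated analysis. The first two require a between-arm comparison of the proportion with a fall of more than 30%. The third attaches paired t tests to the primary outcome and does not plainly assign any between-arm test to that proportion. This conclusion rests on the text and on the exact reproduction of 35 placebo patients, with no outside assumption.

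The size of the consequence does depend on an assumption, the shared improvement d. With no product effect, the chance of a significant paired test in the food arm rises from 14% at d = 0.1 to 99% at d = 0.5. The side-by-side misreading peaks at about 41% near d = 0.3 and falls away on both sides. Because this concerns the trial's main conclusion and can be put right by wording, it should be corrected before the data are analysed.

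**What to change.** In section 2.11:

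1. Name as the primary analysis a two-sided between-arm comparison of the proportion with a fall of more than 30% in MRS-PDFF at week 24, in all randomised patients. Use a χ² test, or logistic regression adjusted for baseline PDFF. Report the risk difference with its 95% confidence interval.
2. Reword the primary endpoint in Table 4 to match section 2.8.1.
3. For continuous outcomes, base efficacy conclusions on a between-arm term: the treatment-by-time interaction in the planned ANOVA, or a baseline-adjusted difference at week 24.
4. Keep the paired t tests as descriptive summaries within each arm.

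The cost is a rewording of section 2.11 and Table 4. No further patients, visits or measurements are needed.

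### Intent-to-treat is declared, but the efficacy methods named need complete data, so as written about 12 of 120 randomised patients would fall out

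*Protocol article*

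**What the plan says.** In the protocol article, Statistical analyses (2.11) opens with the population: "This study will use intent-to-treat patient population". Two methods are then named for efficacy.

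- For repeated measurements: "Repeated measures analysis of variance (ANOVA) will be used for variables measured over time to test treatment efficacy, time, and interaction between them".
- For the change from baseline to week 24: "paired *t* tests will be used for primary and secondary outcomes", with liver fat content in the list that follows.

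Missing data are mentioned once. The sentence begins "Secondary analysis will be performed in all participants who completed 24 weeks of intervention and had a drug intake rate of ≥80" (per cent) and ends with "cases with missing data would be excluded from the analysis".

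Primary endpoints (2.8.1) defines a responder: "The primary endpoint is a decrease in MRS-PDFF by more than 30% from baseline at 24 weeks". Sample size estimation (2.10) plans for dropout: "the total number is about 120 taking into account the 10% shedding rate". Table 3 schedules the liver fat scan at weeks 0, 12 and 24, and the laboratory and anthropometric outcomes at weeks 0, 4, 12, 24 and 36.

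**The concern.** A paired t test cannot use a patient who has no week-24 value. Classical repeated measures ANOVA drops a patient who misses any visit in the model, so for the laboratory outcomes one missed visit out of as many as five is enough. Both methods therefore become complete-case analyses in ordinary use, whatever population is declared. The one sentence on missing data points to exclusion too, and nothing in the article keeps a dropout in an efficacy analysis.

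At stake is the comparison that randomisation protects. If patients who stop are mostly non-responders, removing them raises the observed response rate. If the arms lose such patients at different rates, the difference between arms is distorted as well.

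**Working it through.** **Inputs.** Arms of 80 and 40 (Abstract, Methods). Response 50% and 13%, two-sided α 0.05, β 0.02, 2:1 allocation, 35 placebo patients and 10% dropout (2.10).

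**1. The plan's own figure.** Pooled-variance formula for two proportions, with r = 2 and p̄ = (0.13 + 2 × 0.50)/3 = 0.3767:

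n(placebo) = [1.960 × √(p̄(1 − p̄)(1 + 1/r)) + 2.054 × √(0.13 × 0.87 + 0.50 × 0.50/r)]² / 0.37²
= [1.960 × 0.5935 + 2.054 × 0.4880]² / 0.1369 = 34.2, rounded up to 35.

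Total 3 × 35 = 105, and 105/0.9 = 116.7, so 117. The plan's 35 and about 120 are reproduced.

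**2. Who would fall out.** 10% of 80 is 8 and 10% of 40 is 4: 12 of 120, leaving 72 + 36 = 108.

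**3. Effect on power** (exact binomial, Pearson chi-square on responders):

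| Analysis | Food | Placebo | Difference | Power |
|---|---|---|---|---|
| Completers only, 72/36 | 50% | 13% | 37.0 points | 98.4% |
| All 120, missing = non-response | 0.9 × 50 = 45% | 0.9 × 13 = 11.7% | 33.3 points | 97.9% |

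**4. Effect on the estimate.** The answer depends on who drops out.

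- If dropout is unrelated to response, exclusion is unbiased at 37 points, and counting missing as non-response is conservative at 33.3.
- If 50% and 13% are the rates in all randomised patients and every dropout is a non-responder, exclusion gives 40/72 = 55.6% and 13/0.9 = 14.4%. The difference is then 41.1 points where the truth is 37.

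**5. Effect on type I error.** Assumptions, not figures from the article: 25% true response in both arms, arms of 80/40, loss as a share of the arm (food/placebo), chi-square between arms, nominal 5% two-sided. Results are simulated and reproduce to about 0.1 percentage point.

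| Loss food/placebo | Dropouts | Exclusion | Missing = non-response |
|---|---|---|---|
| 10%/10% | either model below | about 5% | about 5% |
| 15%/5% | all non-responders | 6.1% | about 5% |
| 20%/5% | all non-responders | 7.9% | about 5% |
| 15%/5% | unrelated to response | about 5% | 6.6% |
| 20%/5% | unrelated to response | about 5% | 8.2% |

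In the second and third rows most of the error under exclusion favours food: about 5.0% and 7.2%, against a nominal 2.5% in that tail. If the percentages are instead taken as shares of the non-responders, those tails fall to 4.0% and 5.3%. In the last two rows the excess runs against food, the arm with more dropout.

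**The case against.** Two stronger readings are tempting, and the article supports neither.

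- **That it prescribes removing dropouts from the primary analysis.** By its grammar the exclusion clause belongs to the secondary analysis of adherent completers, where exclusion is normal and does not contradict intent-to-treat. Loss from the main analyses is inferred from the methods named.
- **That the sample size assumes exclusion.** Inflating for 10% dropout is routine and compatible with any missing-data method.

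It can also be said that this is a condensed article, that missing-data detail usually sits in an analysis plan, and that a paired t test or an ANOVA can be run on imputed data. Silence alone would indeed be no finding. But the article does name its methods, and they fit the declared population only if something unstated is added.

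The strongest objection concerns size. No arm-specific dropout rate is given, and under Dosing rationale (2.5) the 12-week pre-test reports no adverse reactions. Unequal loss through intolerance is therefore assumed, and this trial runs twice as long. The calculations also use a between-arm test of responders. The article names chi-square only for baseline variables and adverse events, and its paired t test works within an arm. The missing between-arm test is a separate matter. Whichever test is used, it must be settled how a patient without a week-24 scan counts.

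**Conclusion.** The point holds in a limited form. The declared population and the named efficacy methods do not fit together, and as written about 12 of 120 randomised patients would drop out of the efficacy analyses. This threatens the validity of the intent-to-treat label, not power: the gap is 97.9% against 98.4%. At the planned equal 10% loss, type I error is not inflated either way. The inflation to about 6.1% or 7.9% rests on unequal dropout made up entirely of non-responders, which nothing in the article establishes. It is a reason to fix the method in advance and does not predict bias in this trial.

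**What to change.** - Replace repeated measures ANOVA with a likelihood-based mixed model that uses every observed visit of every randomised patient.
- Analyse the responder endpoint (a fall of more than 30% in liver fat) in all 120 patients as randomised, counting a missing week-24 scan as non-response.
- Add multiple imputation from baseline and week-12 liver fat as a sensitivity analysis. Both scans are already scheduled in Table 3.
- Word the exclusion of missing cases so that it clearly applies only to the analysis of patients with at least 80% intake.

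The cost is a wording change and modest programming, with no new data. Reported response rates will be slightly lower. There is also a real downside: if dropout is unequal but unrelated to response, counting missing as non-response is biased against the arm that loses more (about 6.6% and 8.2% two-sided error in the scenarios above). That is why the imputation analysis should be prespecified beside it.
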